## Current state of the art in clinical care in the relevant field of application and the proposed benefits of the new device

Over the past several decades, mechanical and electrical devices have been used for gait training of patients with neurological disorders. Body-weight-supported treadmill systems (BWST) have shown varying degrees of effectiveness in gait rehabilitation for children with CP. While the advanced robotic exoskeleton with BWST system (e.g. LOKOMAT by Hocoma Inc.) provides a safe and convenient environment for gait training, there is a paucity of wearable exoskeletons for the developmental age preventing from rehabilitation in domiciliary and ecological setting. Recently, few pilot studies demonstrated that overground gait training with wearable exoskeletons in hospital settings is effective in improving gait quality in small groups of children with CP. Other researchers tested an exoskeleton with weight-bearing on children with different diagnosis, demonstrating an increase in the number of steps performed. Furthermore, a case study reported applicability of a robotic-assisted walker for helping a child with quadriplegic CP to walk overground. Finally, a recent review highlighted that robotic exoskeletons have the potential to improve the mobility of CP children and to increase community participation and quality of life and suggest to perform works involving larger controlled intervention studies.

Despite these preliminary works there is a paucity of options and of biomechanical data supporting exoskeleton effectiveness. The Bionic Power Inc. proposes Agilik as a potential solution for gait training of children with crouch gait. Owing to the heterogeneous causes of crouch, they developed a device in which the type of assistance can be optimised and personalised for the individual user. This enhances its potential as a rehabilitative device compared to existing systems.

### Risks and clinical benefits

#### Anticipated Benefit:

Participants to the study could benefit in using the device since the Agilik aids the user in standing, improves walking pattern and reduces crouch and energy expenditure, thus improving gait endurance.

#### Classification of Risk (for the study as a whole):

This study is classified as 45 CFR 46.404 - Research not involving greater than minimal risk to the children. The risks associated with this study are reasonable in relation to the anticipated benefit.

#### Specific Risks:

*Motion capture:* There is a slight risk of falling during the walking tasks, but these should be no greater than those encountered in everyday life. A trained physical therapist will be present at all times during data collection to ensure safety and assist subjects.

*Specific risks related to the use of Agilik:* Known and predictable risks related to the use of the Agilik are reported and described in the IFU from the manufacturer (section 4 of D0476-18\_IFU AGILIK 1.1).

## **Description of the relevance of the clinical investigation in the context of the state of the art of clinical practice**

Wearable devices that provide some type of external assistance and/or support to help a person perform a functional task, often referred to as robotic exoskeletons, are increasingly available as training/assistive devices. However, there is still a lack of evidence supporting their use and for determining optimal methods for specific patient populations.

This study proposes to demonstrate the clinical improvement due to the use of Agilik by Bionic Power in domiciliary setting, for patients with crouch gait due to CP.

## **Objectives and hypotheses of the clinical investigation**

The primary purpose of this study is to improve the clinical use of a powered extension assist knee ankle foot orthosis (Agilik) in individuals with knee extension deficiency due to cerebral palsy in a domiciliary setting. Considering the preliminary data available, we will specifically focus on improvement of anti-gravity knee extension in mid stance (KEMS) and endurance in patients with crouch gait due to CP. Therefore, the primary aim is to compare the KEMS and the endurance at baseline, after 2 months of Agilik training (intervention group) or standard care/daily life activities (control group) and after one month of follow-up.

The secondary aim is to compare the two groups in terms of joint ROM and muscle length, spasticity, postural and motor abilities, gait speed and pattern and self-perceived performance.

Finally, the third aim is to evaluate the usability and the acceptability of the exoskeleton within the intervention group. Also some evidence about the user experience with the technology will be collected, encompassing the subjective perspective of both the patient and the caregivers.

## **Design of the clinical investigation**

### **Duration**

The duration of the investigation will be 24 months. The duration of the study for a single subject will be approximately 6 months.

### **General Information of the protocol**

The clinical investigation will be a study with the following characteristics:

- Confirmatory and Not first-in-human;
- Randomised controlled study;
- Prospective study;
- Multicentric.

### **Endpoints and measured variables**

In order to demonstrate the clinical improvement due to the use of the device, we will consider the following primary endpoints:

- Distance walked during a 6-minutes walking test (6MWT);
- The KEMS measured during gait analysis assessment

---

 Enright, Paul L. "The six-minute walk test." Respiratory care 48.8 (2003): 783-785

In addition, secondary endpoints will be considered with the following purposes:

- at T0 (baseline), T1 (post intervention) and at T2 (follow-up)
  - Measurements of the Joint ROM and muscle lengths
  - To determine the level of spasticity in the lower limbs with the Modified Ashworth scale (MAS)
  - To assess postural and motor abilities with Gross Motor Function Measure-88 (GMFM-88)
  - To assess functional gait assessment (walking speed) with the 10-meter walking test (10mWT)
  - To evaluate kinematics and kinetics assessments (gait pattern) with the 3D gait analysis overground with EMG data acquisition
  - To determinate self-perception of performance in everyday living with Canadian Occupational Performance Measure (COPM)
  - To quantify static balance with Centre of Pressure (COP) detection using the force platforms of the gait analysis lab when available
- at T1 only in the Intervention Group:
  - to assess the usability and acceptability of Agilik in parents/caregivers with the System Usability Scale (SUS) and the Technology Acceptance Method 3 (TAM-3)
  - to investigate aspects of behavioural engagement during the use of the Agilik device at home with semi-structured interviews with patients and their families

Only parents/caregivers of participants in the intervention group will be provided with a diary to freely explore, during the training, their thoughts and feelings about the device, in order to have a more extensive monitoring of the treatment.

Finally, an exploratory outcome will be:

- to perform a remote monitoring of gait behavior with sensorized shoes by Magnes (MAGNES AG, [name]). If possible, during the months between T0 and T1 we will ask the participants of both groups to wear the shoes during indoor and outdoor walking, allowing us to acquire gait data to assess spatiotemporal parameters during daily life.

---

### Information on the investigational device, on any comparator and on any other device or medication to be used in the clinical investigation

During the investigation, different sets of Agilik devices will be used for each of the six clinical experimental centres. They will be uniquely identified through labels reporting their serial numbers. No other devices will be tested. For other information on Agilik, refer to the section “*Device description*”.

### Information on subjects

We will enroll 40 children with knee extension deficiency due to CP according to sample size calculation.

#### Inclusion criteria:

- Volunteer who have a diagnosis of CP and a crouch gait
- Provision of signed and dated informed consent form.
- Stated willingness to comply with all study procedures and availability for the duration of the study, or alternatively, ability to do so based on parent report and physician observation during history and physical examination.
- Age between 5 and 17
- body weight between 20 and 125 Kg
- Knee flexion retraction assessed in supine position by less than 10°. Hamstring contracture as assessed by straight leg raising test does not limit ability to participate in the study.
- Subjects must not have had a tibio-tarsal arthrodesis. In addition, they must have at least 5° of passive dorsi-flexion of the ankle.
- Able to walk at least 3 m without stopping, with or without a walking aid.
- Able to understand and follow simple directions based on parent report and physician observation during historical and physical examination.
- GMFCS level I, II and III
- MAS score  $\leq 2$

#### Exclusion criteria:

- Any severe neurological, musculoskeletal and/or cardiorespiratory involvement preventing the ability to walk;
- A history of uncontrolled seizure in the past year
- Severe spasticity
- Hip and/or knee flexion contracture of more than 20°

Each subject is considered enrolled in the study when he/she (or his/her legal tutor) consents to participate by signing the informed consent. The recruitment will take place at IRCCS Medea, IRCCS

Fondazione Stella Maris, Fondazione Don Carlo Gnocchi Onlus Rome, Fondazione Mondino, Centro S. Maria al Mare - Fondazione Don Carlo Gnocchi and Fondazione Don Carlo Gnocchi - IRCCS S. Maria Nascente.

### Measures to be taken to minimise bias and management of potential confounding factors

Participants to the study will be randomly divided into two groups in order to increase the likelihood that other variables, not taken into account in the study design, are evenly distributed within the two groups (randomised study).

All the procedures will be standardised to ensure repeatability of the collected measures and minimise operators' errors. The devices used to assess gait analysis and balance will be calibrated to ensure measurement repeatability.

### Procedures

This is a study of subjects with CP to demonstrate the clinical improvement due to the use of Agilik in children with knee extension deficiency due to cerebral palsy (see Figure 1 in section *Synopsis of the clinical investigation*). Participants will be enrolled based on inclusion and exclusion criteria and medical/physical history. Included children will be randomly divided into two groups (hereafter Intervention and Control Groups), stratified according to GMFM and gender, for a randomised control study. Both groups will start signing the informed consent.

The first visit is for physical examination and T0 assessments, which will include:

- 6MWT and KEMS measured during gait analysis, for demonstrating the clinical improvement due to the use of the device
- GMFM for postural and motor assessment
- 10mWT for functional gait assessment
- MAS to evaluate the level of spasticity in the lower limbs
- Joint ROM and muscle lengths examination performed manually by a medically responsible individual
- 3D gait analysis overground with EMG
- COPM for self-perceived performance assessment
- COP detection to quantify static balance.

Then, the Control Group will continue with standard therapy and daily life activities, and we will ask the participants to wear the sensorized shoes by Magnes during their outside walking when possible.

On the other hand, the Intervention group will start the intervention, which consists of:

1. 3 visits dedicated to exoskeleton preparation at the orthopedic center (casting for brace fabrication, set-up and calibration of the system).
2. Training with Agilik (4-5 weeks, 2 sessions/week) during which patients will practice walking with the device. Also the families will be trained to be able to autonomously use the system during home rehabilitation.
3. Home rehabilitation (2 months, 30 minutes/day, 5 days/week) during which subjects will practice walking with the device at home. Moreover, we will ask the participants to wear the sensorized shoes by Magnes during their outside walking when possible. Furthermore, children/parents will be asked to fill a diary to assess engagement in using this device.

Finally, 3 months after T0, both groups will undergo the outcome assessments (T1), and the follow-up assessments (T2) one month after T1. The follow-up assessment coincides with T0 assessments, while outcome assessments add, only for the Intervention Group, usability and acceptability evaluation of Agilik (SUS and TAM-3). Semi-structured interviews with patients and their families will be performed at/after T1 in the Intervention group to investigate aspects of behavioral engagement during the use of the Agilik device at home.

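### T1 is set at 3 months after T0, but brace preparation, supervised training and 2 months of home use do not fit into that interval

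*Protocol*

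**What the plan says.** In the protocol, Procedures, baseline comes first: "The first visit is for physical examination and T0 assessments, which will include" the primary and secondary measures. Only then does the device arm begin: "On the other hand, the Intervention group will start the intervention, which consists of" three numbered steps.

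1. Preparation: "3 visits dedicated to exoskeleton preparation at the orthopedic center (casting for brace fabrication, set-up and calibration of the system"). No duration is given.
2. Supervised training: "Training with Agilik (4-5 weeks, 2 sessions/week) during which patients will practice walking with the device". Families also learn to operate the system here, for use at home.
3. Home phase: "Home rehabilitation (2 months, 30 minutes/day, 5 days/week) during which subjects will practice walking with the device at home".

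The section closes by fixing the later visits: "Finally, 3 months after T0, both groups will undergo the outcome assessments (T1), and the follow-up assessments (T2) one month after T1".

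Three other sections bear on the timing:

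- Endpoints and measured variables labels T1 as the post-intervention assessment and T2 as follow-up.
- Objectives and hypotheses places the primary comparison "after 2 months of Agilik training (intervention group) or standard care/daily life activities (control group"), and again after a month of follow-up.
- Duration says: "The duration of the study for a single subject will be approximately 6 months".

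**The concern.** The three steps can only run in sequence. Device description (Design) says that each orthosis is made for the individual patient, so supervised training has to wait for the brace. Home use has to wait for the family training in step 2. The interval from T0 to T1 must therefore hold all three steps, yet it is barely long enough for the last two.

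Both primary endpoints, the 6-minute walk distance and knee extension in mid stance, are read at T1. If T1 stays at 3 months, they are measured on a partly delivered intervention, and the shortfall varies with how long each child's brace takes. The meaning of T2 is then also unclear. It is a one-month post-training visit if home use stops at T1, but not if home use continues past T1, and the protocol does not say which. The usability and acceptability measures taken at T1 could likewise precede the end of home use. Six centres could each resolve the conflict in their own way, so that T1 would not mean the same thing across sites.

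**Working it through.** **Inputs (protocol, Procedures).** T1 = T0 + 3 months; T2 = T1 + 1 month; training = 4 or 5 weeks; home phase = 2 months; preparation = P weeks, not stated.

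**Conversion.** 1 month = 365.25 / 12 / 7 = 4.348 weeks, so 3 months = 13.04 weeks and 2 months = 8.70 weeks.

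**Reproducing the 3 months.** With 4-week months, 4 weeks of training and P = 0, the total is 4 + 8 = 12 weeks, which is exactly three 4-week months. The stated interval is thus recovered from steps 2 and 3 with preparation left out.

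**Time left for preparation** = interval to T1 - training - home phase:

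| Month convention | Training 4 weeks | Training 5 weeks |
|---|---|---|
| Calendar months throughout | 13.04 - 12.70 = +0.35 week | 13.04 - 13.70 = -0.65 week |
| 4-week months throughout | 12 - 12 = 0 | 12 - 13 = -1 week |
| Most lenient: calendar 3 months, 8-week home phase | 13.04 - 12 = +1.04 weeks | 13.04 - 13 = +0.04 week |

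(The +0.35 is from unrounded values.) The best case leaves about 1 week for three visits and the making of a custom brace.

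**Illustration of the shortfall.** The values of P are assumptions. Home weeks before T1 = 13.04 - P - training. All device-training weeks before T1 = 13.04 - P, out of 12.70 or 13.70.

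| Assumed P | Home weeks done (share of 8.70) | Share of all device-training weeks |
|---|---|---|
| 2 weeks | 6.04 to 7.04 (70-81%) | 11.04/13.70 to 11.04/12.70 (81-87%) |
| 4 weeks | 4.04 to 5.04 (47-58%) | 9.04/13.70 to 9.04/12.70 (66-71%) |

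**When the described intervention would end** = (P + training)/4.348 + 2 months after T0. P = 2 gives 3.4 to 3.6 months and P = 4 gives 3.8 to 4.1 months. A T2 one month later would fall at 4.4 to 4.6 or 4.8 to 5.1 months.

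**Time per child.** T0 to T2 as written is 3 + 1 = 4 months, against about 6 months under Duration.

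**The case against.** Several points on the other side are sound.

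- **Duration.** A reader might infer that 6 months against 4 is an outright contradiction. It is not firm. Enrolment starts at signed consent, and the time from consent to T0 is not stated, so it may account for part of the gap.
- **Objectives.** The 2 months of Agilik training need not mean home weeks only, because step 2 is itself called training with the device. With an assumed 4 weeks of preparation a child would have 13.04 - 4 = 9.04 weeks of device training by T1, more than 8.70. On that reading the objective is met.
- **Size.** The percentages rest on a preparation time that no section gives. Counting home weeks alone gives the larger loss and counting all training weeks the smaller. Home sessions are more frequent (5 days against 2 sessions a week), so neither measure is the whole answer.
- **Timing by arm.** A reader might infer that growth or natural change is confounded with arm. As written, both groups are assessed 3 months after T0, so the comparison is not biased by unequal timing. A later T1 in the intervention arm alone would arise only if sites departed from the protocol to let training finish.
- **Extreme scenarios.** One might assign the whole 2-month gap under Duration to preparation and conclude that almost no home training would be done by T1, or that T1 would fall at about 5 months in one arm and 3 in the other. Nothing in the protocol says that the gap is preparation.
- **Figure 1.** The study-design figure is not available here and may show where preparation sits. It could not remove the conflict within the text of Procedures.

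None of this answers the core arithmetic: preparation follows T0, and the two later steps already fill the interval.

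**Conclusion.** The conflict is real and lies within Procedures: the intervention described after T0 does not fit before the T1 stated there. This follows from the protocol's own figures, with +0.35 to -0.65 week left for preparation and about 1 week at best. It needs no assumption beyond the steps being sequential, which the custom brace and the family training imply. T1 as scheduled therefore cannot be relied on as the post-intervention assessment that the endpoints section calls it.

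How much training would be missing cannot be determined, because preparation time is not given; the shares for an assumed 2 to 4 weeks are illustrations. The statements under Objectives and Duration are supporting signs that the timeline was not reconciled, not separate contradictions. The text as it stands does not support a claim of bias from unequal assessment times. Because the primary assessment is affected and the correction is inexpensive, it should be made.

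**What to change.** Reconcile Objectives and hypotheses, Duration, Endpoints and measured variables, and Procedures (and Figure 1 if it shows the timeline) so that they describe one schedule. State how long preparation is expected to take. Keep T0 as the anchor, since it is the baseline for the within-group comparisons under Statistical considerations. Set T1 and T2 at the same elapsed time from T0 in both arms, at a time by which the described intervention, including preparation, can be complete. State whether home use ends at T1, so that T2 has a defined meaning. The content and length of preparation, training and home use are for the sponsor and clinical team to decide.

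The cost is protocol wording and control-arm visits moved by some weeks. With the assumed 2 to 4 weeks of preparation, T2 would fall at 4.4 to 5.1 months after T0, which is below the 6 months per child already stated, subject to the time taken between consent and T0.

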### Monitoring plan

The investigator undertakes to ensure that the planned procedures and actions comply with the code of good clinical practice - GCP and the applicable regulations.

The Principal Investigator of each clinical site is responsible for data and safety monitoring for this protocol. Patient tolerance with Agilik setup and data collection process will be evaluated during the experimentation. Subjects will be informed that they can ask to stop the experiments at any time.

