#### Materials coming into contact with the human body

The Agilik is a robotic knee hinge integrated in a custom KAFO; the Agilik itself is not in direct contact with the skin or with the human body. For further information, see the Instruction for Use attached to the protocol (D0476-18\_IFU AGILIK 1.1).

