### **Safety reporting**

Pursuant to EU Regulation 2017/745, MDCG 2020-10/1 Rev1 (Safety reporting in clinical investigation of medical devices under the Regulation EU 2017/745), Legislative Decree 46/97, Legislative Decree 507/92, Meddev Guideline 2.12-1 rev.8 and its supplement "Additional guidance regarding the vigilance system as outlined in MEDDEV 2.12-1 rev.8," all incidents and serious adverse events that may occur during the investigation should be reported to Office V (Medical Device Vigilance) of the DGDFSC of the Ministry of Health and the relevant Ethics Committee. Since this is a clinical study, serious adverse events may also be forwarded to Office VI of the Ministry of Health for information.

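### Non-serious falls, skin injury and pain in the home phase, where about 75–85% of device sessions take place, are not actively collected, and not equally in both arms

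*Protocol*

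**What the plan says.** Device exposure is set out in the protocol's Procedures section. The intervention arm first has "3 visits dedicated to exoskeleton preparation at the orthopedic center (casting for brace fabrication, set-up and calibration of the system"), then "Training with Agilik (4-5 weeks, 2 sessions/week) during which patients will practice walking with the device", then "Home rehabilitation (2 months, 30 minutes/day, 5 days/week) during which subjects will practice walking with the device at home". T1 follows three months after T0, and T2 one month after T1. Controls continue standard therapy and daily life, with no study contact scheduled between T0 and T1.

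Staff observation is described for the clinic. On motion capture, Specific Risks says "A trained physical therapist will be present at all times during data collection to ensure safety and assist subjects". Ethical considerations adds supervision during test procedures and a therapist at clinical-site sessions. The Monitoring plan makes each site's principal investigator responsible for safety monitoring and adds "Patient tolerance with Agilik setup and data collection process will be evaluated during the experimentation", with no instrument or schedule.

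For the home phase, Endpoints and measured variables says that carers in the intervention group only "will be provided with a diary to freely explore, during the training, their thoughts and feelings about the device", and gives wider monitoring of the treatment as the reason. Procedures describes the diary as a measure of engagement.

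Event reporting is covered in two places. Under Safety reporting, "all incidents and serious adverse events that may occur during the investigation should be reported to Office V" (of the Ministry of Health) and to the ethics committee. Under Accountability regarding the device, researchers contact the manufacturer or distributor after a malfunction or any adverse event.

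**The concern.** The trial sets out to show benefit from home use of a powered orthosis in children who walk with a crouch gait. Most of the walking in the device takes place away from study staff, yet no form or scheduled question asks families whether the child fell, had skin marks or developed pain. A non-serious event reaches the data only if someone chooses to mention it.

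The opportunity to mention it also differs by arm. Intervention families meet study personnel repeatedly, keep a diary and are interviewed at or after T1. Control families have none of these. Children with crouch gait may also fall without the device, so a count drawn mostly from one arm cannot separate background falls from a device effect. This is a matter of what is collected, and no statistical analysis plan can recover events that nobody asked about.

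**Working it through.** The protocol states no home share and no expected event rate, so there is no figure of its own to reproduce. The check has three parts.

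**1. Share of device sessions at home.** Inputs from Procedures:
- Training sessions C = 2 × 4 to 2 × 5 = 8 to 10, read here as supervised at the clinical site.
- Home sessions H = 5 × w, where w is the number of weeks in two months. I take w from 8 to 9; the calendar value is 2 × 30.44 / 7 = 8.7.
- Preparation visits: 3. These are casting, set-up and calibration rather than walking practice, so the share is shown with and without them.

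| w | Training weeks | H | C | H/(H+C) | H/(H+C+3) |
|---|---|---|---|---|---|
| 8 | 5 | 40 | 10 | 80.0% | 75.5% |
| 8 | 4 | 40 | 8 | 83.3% | 78.4% |
| 8.7 | 5 | 43.5 | 10 | 81.3% | 77.0% |
| 8.7 | 4 | 43.5 | 8 | 84.5% | 79.8% |
| 9 | 5 | 45 | 10 | 81.8% | 77.6% |
| 9 | 4 | 45 | 8 | 84.9% | 80.4% |

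The share is 80–85% without the preparation visits and about 75–80% with them. At 30 minutes a session, home walking comes to 40 × 0.5 = 20 h to 45 × 0.5 = 22.5 h per child.

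These are planned figures, and the timetable is tight. Three months is 3 × 30.44 / 7 = 13.0 weeks. Five weeks of training plus 8.7 weeks at home is 13.7 weeks, which does not fit. Four weeks plus 8.7 is 12.7, which leaves 0.3 weeks for preparation. If the home phase shrank to 7 weeks (an assumption), the share would be 35/(35 + 10) = 77.8%, or 35/(35 + 10 + 3) = 72.9% with preparation visits. Home would still be the main exposure.

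**2. Scheduled study contacts between T0 and T1.** Intervention: 3 + 8 = 11 to 3 + 10 = 13. Control: 0.

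**3. What each home-phase or post-baseline source records.**
- Diary: intervention arm only, free text on reactions to the device and engagement.
- Sensorized shoes: both arms, where possible; gait parameters, not events.
- SUS, TAM-3 and interviews at or after T1: intervention arm only; usability, acceptability and engagement.
- Listed assessments at T0, T1 and T2: both arms; no question on adverse events, falls or skin. The manual joint and muscle examination might bring a problem to light, but it is not set up to record one.
- Safety reporting: both arms and any place, limited to incidents and serious adverse events. It says where events are sent, not how families are asked.
- Device accountability: any adverse event, but the action is contact with the manufacturer or distributor, who arranges repair. It describes no participant-level record.

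None of these routes actively asks both arms about non-serious events.

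**The case against.** The strongest reply is that the protocol does provide for safety. Reporting of incidents and serious adverse events has no limit of place or arm. Any adverse event known to the researchers prompts action. The site investigator's responsibility for safety covers the whole protocol, and the tolerance sentence does not expressly exclude the home. The diary has a stated treatment-monitoring purpose, Conditions of Use require adult supervision of children, and families are trained. This is also a post-market study of a Class 1 device, classified as minimal risk, and safety is not among its stated aims.

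Much of this stands, and it rules out some stronger readings. A reader might infer that home events go unrecorded, that they have no route into the study, or that the trial would have no usable home safety data. The documents do not support that: a serious fall at home is reportable, and a lesser event can be passed on.

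A reader might also set the statement that "the Agilik itself is not in direct contact with the skin or with the human body" against the Applied Parts list, which includes the KAFO shell and straps, and infer that skin risk is overlooked. That does not follow. The first statement concerns the robotic hinge and the second the custom shell. Known device risks are placed in the instructions for use, which are not available here.

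Finally, the sample gives weak safety inference even with full capture. With 20 children per arm (assuming 1:1 allocation of 40), zero events excludes only rates above 1 − 0.05^(1/20) = 13.9% (one-sided 95%). That argues for a descriptive listing rather than a test. It does not argue for unequal collection. All the routes above still depend on an event reaching the researchers, and only one arm has regular study contact.

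**Conclusion.** The point holds as a cheap improvement, not as a failure of safety reporting. Non-serious falls, skin injury and pain during the two-month home phase would be captured passively, and more readily in the intervention arm, so the events that are captured could not be compared fairly between arms. The phase concerned holds roughly 75–85% of planned device sessions, and scheduled contacts between T0 and T1 are 11–13 against none.

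This rests on two months being 8–9 weeks, on the training sessions being supervised, and on the home phase running as planned. The contact count covers study contacts only, since controls continue to see their usual therapists. How many events would be missed cannot be estimated from the documents.

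**What to change.** - **Diary (Endpoints and measured variables; Procedures).** Keep the free-text page for engagement. Add a short structured section on falls, skin marks, new pain, device faults and minutes walked with the device. Give the falls and pain items to control families as well.
- **T1 and T2 visits (Procedures).** Ask both arms the same adverse-event questions and enter the answers in REDCap.
- **Monitoring plan.** Extend the tolerance sentence to cover the home phase, and say who reviews the entries and when.
- **Safety reporting and device accountability.** State that non-serious adverse events are recorded per participant in both arms.
- **Reporting.** List all adverse events by arm, descriptively.

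The cost is one CRF page, amendment wording and a small recording burden on control families, with no extra visits. Regular phone calls are optional: every two weeks from T0 to T1 (about 6) plus one before T2 would be about 7 × 40 = 280 calls, and would add contact to a usual-care arm. The fix does not depend on them.
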